### Blinding

Randomization and group allocation will be blinded for the data collectors of this RCT.

### Implementation

Process evaluation will include fidelity of the implementation, consistency of the implementation across ECEC services, and barriers to implementation. To assess fidelity and consistency of the intervention, educators will complete a weekly checklist documenting the activities that were undertaken in the ECEC centre. During the intervention period educators will receive monthly visits from the research team for process evaluation. During these visits we will assess objective information on the sitting time in a small random sample (10 %) of toddlers to monitor the implementation of the intervention. On these occasions we will also assess the educators’ perceived barriers of the intervention implementation with semi-structured interviews. Attendance rates for each child will also be collected to account for the dose of intervention received.

### Data Management

In compliance with the University’s policies, all study-related information will be stored securely at the University, in locked filing cabinets in locked offices, and will be treated as strictly confidential.

Data will be entered directly into existing, secure online or offline databases. All databases are secured by password-protected access systems. For quality control of data entry, another member of the research team will do a random check of data entry quality in 10 % of sample cases. The confidentially and anonymity of the data will be secured through a coding system of the participants. Re-use of the anonymised data will be made available for future projects by arrangement. All participants will also have access to their own results. A data monitoring committee will not be established due to the fact that the interventions poses no risk to the participants.

### Statistical analysis

#### Primary analysis

Analysis of the primary outcome will be conducted using a linear or generalized mixed model in STATA 14.0 (or higher). The mixed model will contain a random effect for time and service nested within group. Degrees of freedom will be altered manually in the code to adjust for the effect of clustering. These established procedures are well documented by Murray [97] and have been used previously by our research institute to analyse a similar study in primary schools [98]. No interim analyses are planned.

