**Methods/Design:**

We will implement a 12-months 2-arm parallel group cluster randomised controlled trial (RCT) with Australian toddlers, aged 12 to 26 months at baseline. Educators from the ECEC services allocated to the intervention group will receive professional development on how to reduce sitting time while children attend ECEC. Participants’ cognitive development will be assessed as a primary outcome, at baseline and post-intervention, using the cognitive sub-test from the Bayley Scales of Infant and Toddler Development.

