In this context, and in an attempt to respond to recent calls on innovative approaches and fresh thinking on how to improve cognitive development in disadvantaged children [21], the primary aim of this study is to assess the effects of reducing sitting time during ECEC on cognitive development, in a cluster randomised controlled trial with toddlers from low socio-economic families. It is hypothesized that at 12-month follow-up, toddlers in centres allocated to the intervention group will have improved their cognitive development by 0.5 SD more than toddlers in ECEC centres randomly allocated to the control group. The secondary aims are to examine the effects of reducing sitting time on toddler’s cardiovascular health and bone density.

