### Assessment of the Outcomes

Data collection will occur at baseline (before randomization) and at the end of the intervention (Fig. 3 Participants Timeline). For those children who have turned 3 at follow-up, an additional four executive function tasks will be collected as described below. Trained research assistants blinded to group allocation will collect all data.

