### Sample Size

#### Sample size and power calculations

We anticipate an effect size of 0.5 for the between-group difference in cognitive development and an intraclass correlation (ICC) of 0.01–0.05. The proposed design has 16 services (8 per group) and 16 children completing per service. Allowing for participation of 18 eligible children with two dropouts per service [10 %] gives a total sample size of 256. This reduces to an effective sample size of 200–254 (with rounding) based on ICCs of 0.05−0.01. The power to detect an effect size of 0.5 with these sample sizes ranges from 0.87–0.96 at an alpha level of 0.05.

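### The primary model lists time as a random effect and names no child effect or baseline adjustment, although each child is tested twice; the follow-up Bayley score should be adjusted for baseline

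*Protocol article*

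**What the plan says.** All places are in the protocol article.

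- **Primary analysis** gives the structure of the model: "The mixed model will contain a random effect for time and service nested within group". It adds "Degrees of freedom will be altered manually in the code to adjust for the effect of clustering", and says that the procedures follow a methods reference and "have been used previously by our research institute to analyse a similar study in primary schools". It lists no fixed effects, no child-level term and no baseline covariate.
- **Abstract, Methods/Design:** "cognitive development will be assessed as a primary outcome, at baseline and post-intervention". The primary outcome is therefore measured twice in a cohort.
- **Assessment of the Outcomes:** "Data collection will occur at baseline (before randomization) and at the end of the intervention".
- **Background**, hypothesis: intervention toddlers "will have improved their cognitive development by 0.5 SD more than toddlers in ECEC centres randomly allocated to the control group".
- **Sample size and power calculations** assumes a standardised effect of 0.5 and an ICC between 0.01 and 0.05. On the layout it says: "The proposed design has 16 services (8 per group) and 16 children completing per service".

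**The concern.** The random effects as written do not match the design in two respects.

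1. Baseline and 12 months are two fixed, planned occasions. A variance for time would rest on two points. The shift over a year of development and its difference between groups are what the trial wants to estimate, so time and group-by-time belong in the fixed part.
2. With random effects for time and service only, a child's two scores count as independent given service. The correlation within a child is ignored, and the standard error of a difference in change depends directly on that correlation.

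Setting the degrees of freedom by hand does not help. It changes the reference distribution, but neither the estimate nor its standard error.

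At stake is the single confirmatory test in a trial of 16 services. A misstated standard error mostly costs power. Leaving the pre-randomisation score out as a covariate gives up precision that costs nothing to obtain.

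**Working it through.** **Inputs from the article.** k = 8 services per group, m = 16 completing children per service, effect 0.5 SD, ICC (ρ) 0.01 and 0.05, alpha 0.05 (taken as two-sided), two waves.

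**Assumptions.** The article gives no baseline to follow-up correlation, so r = 0.3, 0.5 and 0.7 are used, equal at child and service level. Variance is 1 at each wave. Degrees of freedom are 16 − 2 = 14; the article gives no number.

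**Step 1: the plan's own power.** The design effect is 1 + 15ρ, which is 1.15 and 1.75. Then 256/1.15 = 222.6 and 256/1.75 = 146.3. Normal-theory power is 0.96 and 0.86, against 0.96 and 0.87 stated, so the stated power is reproduced closely. The stated effective sizes of 254 and 200 are not reproduced; that is a separate matter and is not used here. This is a single-wave comparison; on 14 df it gives 0.93 and 0.80.

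**Step 2: standard errors.** Write V = ρ + (1 − ρ)/m.

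- True SE of the difference in change: √[(4/k)(1 − r)V]. For ρ = 0.01 and r = 0.5: √[0.5 × 0.5 × 0.071875] = 0.134.
- SE reported with fixed group, time and group-by-time, random service and no child effect: √[4(1 − ρ)/(mk)]. This is √(3.96/128) = 0.176 and √(3.80/128) = 0.172. It does not contain r, which is the defect.
- SE with baseline as covariate: √[(2/k)(1 − r²)V]. Its variance is (1 + r)/2 times that of the change analysis, so 0.65, 0.75 and 0.85 for the three correlations. It is smaller for any r below 1.

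**Step 3: results.** Type I error and power without a child effect are simulated (4,000 runs per cell); the other powers are closed-form on 14 df.

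| ρ | r | True SE | SE, no child | Ratio | Type I, no child | Power, no child | Power, valid change | Power, baseline-adjusted |
|---|---|---|---|---|---|---|---|---|
| 0.01 | 0.3 | 0.159 | 0.176 | 1.11 | 0.023 | 0.77 | 0.83 | 0.95 |
| 0.01 | 0.5 | 0.134 | 0.176 | 1.31 | 0.005 | 0.83 | 0.93 | 0.98 |
| 0.01 | 0.7 | 0.104 | 0.176 | 1.69 | 0.000 | 0.88 | 0.99 | 0.998 |
| 0.05 | 0.3 | 0.196 | 0.172 | 0.88 | 0.058 | 0.75 | 0.66 | 0.84 |
| 0.05 | 0.5 | 0.165 | 0.172 | 1.04 | 0.026 | 0.79 | 0.80 | 0.90 |
| 0.05 | 0.7 | 0.128 | 0.172 | 1.35 | 0.003 | 0.84 | 0.95 | 0.98 |

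Simulated type I error is 0.047 to 0.052 for the baseline-adjusted analysis and 0.048 to 0.054 for the valid change analysis (service-mean changes).

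**Step 4: if time means service-by-time.** Without a child effect, the expected service-by-time mean square is (1 − r)(1 + 15ρ). At ρ = 0.01 it is 0.81, 0.58 and 0.35 against a residual of 0.99. At ρ = 0.05 it is 1.23, 0.88 and 0.53 against 0.95. In five of the six cells it falls below the residual, so a fit that bounds variances at zero drops the term and the SE stays too large. The exception is ρ = 0.05 with r = 0.3.

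**Step 5: sensitivity.** A second simulation (3,000 runs per cell) made half of the service variance service-by-time. Without a child effect, type I error was 0 to 2.6%, and power 0.77 to 0.88 (ICC 0.01) and 0.69 to 0.81 (ICC 0.05). The baseline-adjusted analysis gave 0.96 to 0.99 and 0.85 to 0.94, with type I error 4.4 to 5.1%.

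**The case against.** The article condenses a fuller plan. The sentence says what the model will contain, not that it contains nothing else, and it lists no fixed effects at all, so it is a partial description. It points to a methods reference and an earlier trial that may give the rest. The phrase about time can be read as service and service-by-time effects within group, which is a sound structure. The loss from omitting the child effect is mostly conservative. A group-by-time model matches the wording of the hypothesis, so preferring a baseline covariate could be called taste.

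Much of this stands. The service-by-time reading is legitimate. A child term may appear in a document not shown. The standard error is not always too large. A correctly specified group-by-time model is valid.

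A reader might also infer that the planned analysis halves the effect. If the group main effect over both waves were tested, the expected estimate would be (0 + 0.5)/2 = 0.25 SD, with power 0.47 to 0.58 at ICC 0.01 and 0.33 to 0.42 at ICC 0.05. The article does not support that inference: it nowhere says that this term is the test, and the hypothesis on improvement argues against it. It is a risk of the wording, not the stated analysis.

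What does not stand is that nothing needs changing. The article chose to state the random effects, and as stated they do not fit two scores per child; nothing else in it corrects them. The service-by-time reading alone does not repair the standard error in most cells. The gain from baseline adjustment is concrete.

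**Conclusion.** The point holds as a misspecified and improvable primary model. As worded, time sits in the wrong part of the model and within-child correlation is not represented. Fitted that way with a group-by-time contrast, the reported standard error is 1.04 to 1.69 times the true one in five of six cells, with type I error below 3%. In the sixth it is 0.88 times, with type I error about 0.058. This is mainly a loss of power, not a general inflation of false positives.

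Adjusting the follow-up score for baseline was more powerful than a valid change analysis in every cell. Because baseline precedes randomisation, both target the same between-group difference.

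The sizes rest on the assumed correlations, on equal correlation at child and service level, and on 14 df. The direction of the gain from baseline adjustment does not depend on which of the assumed correlations is right.

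**What to change.** State the primary analysis as a linear mixed model for the follow-up Bayley-III cognitive score, with fixed effects for group and baseline score and a random intercept for service. Test the group effect on between-service degrees of freedom, and give the number (14 if services minus groups).

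If a two-wave model is preferred, specify fixed group, time and group-by-time, with random effects for service, service-by-time and child within service, and name group-by-time as the primary test.

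Age at assessment may be added as a covariate, but it is optional and not part of this correction.

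The cost is a change of wording before outcome data are analysed. Both scores are already collected, and no change to recruitment or assessment is needed.

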#### Secondary analyses

Mixed models will also be used to analyse the differences between treatment and control groups for all continuous secondary outcome variables.

#### Mediation and moderation analyses

Two types of analyses will be conducted to explore the theoretical assumptions of the intervention. First, hypothesised mediators of change in cognitive development (e.g., educator self-efficacy) will be examined using multilevel linear analysis and a product-of-coefficients test appropriate for cluster RCTs. Potential moderators of the intervention effects (e.g., child age and gender) will also be explored using multi-level modelling.

## Discussion

Evidence suggests that early childhood development is critical for the establishment of the foundations for future learning, and social and health outcomes [6, 7] and even small improvements in cognitive development and EF during early childhood “could shift the entire distribution of outcomes in a salutary direction and yield large improvements in health, wealth and crime rate for a nation” [8]. The proposed RCT represents the first study aimed to assess the effects of decreased sitting on cognitive development and EF in toddlers. The results of this study could significantly inform SB and PA guidelines for the early years, as SB experimental studies and studies with toddlers using objectively-measured SB and PA have been identified as critical to enhance the quality of the evidence base [99, 100]. Moreover, research regarding the potential harms of excessive sitting and benefits of PA in toddlers are scarce [32, 44] and a call has been made for further research on cognitive and psychosocial development to inform SB guidelines for the early years due to the lack of evidence in this area [101]. This RCT aims to address this knowledge deficit.

This RCT will also take an innovative approach and use unique methodologies to significantly increase current understanding. In children SBs such as television viewing and overall screen time have been commonly studied and rely on parent-proxy reports; however, they do not represent the total amount of habitual sedentary time. This project will provide new insights on SB and cognitive development in toddlers by: (i) including direct comprehensive and standardized measures of cognitive development for young children; (ii) objectively assessing SB and PA with accelerometry (iii) testing independent associations of SB and cognitive development (e.g. adjusting the analysis for PA levels); (iv) testing mediators of change in cognitive development and moderators of the intervention effects and (v) using a cluster RCT design which is critical for establishing cause and effect relationships and dose-response associations.

Through better understanding of the effects of reducing sitting time on cognitive development and EF in disadvantaged toddlers, this RCT has the potential to inform programs and policies designed to optimize developmental and health outcomes in young children, specifically in those from a disadvantaged backgrounds.

This project has the potential to inform future government policies and programs focused on SB and PA such as updating the National Physical Activity Recommendations for Children 0–5 years [102].

In conclusion, the knowledge generated by this project could be beneficial, nationally and internationally, for: i) parents aiming to optimize developmental outcomes for their children; ii) early childhood educators, clinicians, health care providers, and health promoters, aiming to enhance developmental outcomes in young children through intervention programs; iii) government departments seeking to develop evidence-based guidelines; and iv) researchers seeking to evaluate and translate effective programs to give young children the best start in life.

## Abbreviations

ECEC: Early childhood education and care
EF(s): Executive function(s)
PA: Physical activity(ies)
SB: Sedentary behavior(s)
